## Abstract

**Background:**

Chronic low back pain is one of the four most common diseases in the world with great socioeconomic impact. Supervised exercise therapy is one of the treatments suggested for this condition; however, the recommendation on the best type of exercise is still unclear. The Pilates method of exercise is effective in reducing pain and disability in these patients, as well as the analgesia promoted by interferential current. Currently, the literature lacks information on the efficacy of the association of these two techniques in the short- and medium-term than performing one of the techniques isolated. The objective of this study will be to evaluate the efficacy of adding interferential current to the Pilates method exercises for the treatment of patients with chronic nonspecific low back pain in the short- and medium-term.

**Methods/Design:**

This study will be a randomized controlled trial with two arms and blinded evaluator, conducted at an outpatient Physical Therapy Department in Brazil. Patients with nonspecific chronic low back pain and pain equal to or greater than 3 in the Pain Numerical Rating Scale (0/10) will be randomly assigned to one of two groups: Group with active interferential current + Pilates (n = 74) will be submitted to the active interferential current associated to the modified Pilates exercises, and Group with sham interferential current + Pilates (n = 74) will be submitted to the sham interferential current associated with the modified Pilates exercises during 18 sessions. The outcomes pain intensity, pressure pain threshold, general and specific disability, global perceived effect and kinesiophobia will be evaluated by a blinded assessor at baseline, six weeks and six months after randomization.

**Discussion:**

Because of the study design, blinding of the participants and the therapists involved in the study will not be possible. The results of this study could contribute to the process of clinical decision- making for the improvement of pain and disability in participants with nonspecific chronic low back pain.

**Trial registration:**

ClinicalTrials.gov NCT01919268

**Electronic supplementary material:**

The online version of this article (doi:10.1186/1471-2474-15-420) contains supplementary material, which is available to authorized users.

## Background

Nonspecific low back pain is characterized by a mechanical pain of musculoskeletal origin, which lasts more than 12 weeks with no defined cause [1, 2]. The prognosis is considered moderately favorable, since 41% of the patients will be recovered by the end of the 12 months [3]. It is known that the shorter the period of chronicity of the low back pain, the greater the patient’s improvement regarding pain and disability [4]. In addition to the global prevalence estimated in 31% [5], low back pain is one of the four most common diseases around the world and is the leading cause of years lived with disability in developed countries [6]. In the United States, it is estimated that the direct and indirect costs [7] for treating this condition is about 84.1 to 624.8 billion dollars; therefore, it is a disease of great socioeconomic impact and the search for the most effective treatment is essential.

Supervised exercise therapy has been recommended by clinical practice guidelines as an effective intervention for the treatment of people with chronic low back pain [1, 8]. However, the most effective type of exercise is still unclear. The Pilates method of exercise is among the array of exercises available for the physical therapy practice. There are several systematic reviews on the use of the Pilates method in the treatment of low back pain, however the results on the effects of this technique are still conflicting. A recent systematic review [9] aimed to provide an update on the effectiveness of the Pilates method in the treatment of patients with chronic low back pain, as several relevant clinical trials were published in the last months. The review concluded that Pilates method exercises show a statistically significant improvement in pain and disability in the short-term and a clinically significant improvement in pain compared to usual care and physical activities. However, the Pilates method showed an equal effect compared to other forms of exercise and massage therapy, although these results are still conflicting.

Another resource widely used in clinical practice, as an adjunct in the treatment of low back pain, is the interferential current [10–15]. The interferential current is an alternating electric current of medium frequency and with amplitude-modulated at a low frequency [16]. Currently, there is a lack of studies investigating the mechanisms of analgesic action of interferential current, but the theory most often cited to explain the modulation of pain by interferential current is the gate control theory [17]. This theory suggests that stimulation of afferent fibers of large diameter (Aβ) promotes the activation of local inhibitory circuits of the dorsal horn of the spinal cord and thus, prevents the pain impulses carried by small diameter fibers (C and Aδ) to reach higher centers [18]. Studies have shown that analgesic electrical currents, whether of low or medium frequency, may reduce pain in patients with chronic low back pain in the short-term [12, 19–21]. However, current evidence on the efficacy of the association of interferential current therapy and supervised exercise, such as the Pilates method, are lacking.

Therefore, the primary objective of this study will be to evaluate whether the association of interferential current with Pilates exercises changes pain and disability in patients with nonspecific chronic low back pain in the short-term. The secondary objective will be to evaluate if the treatment changes specific disability, kinesiophobia and global perceived effect in the short- and medium-term, and pain and disability in the medium-term. The hypothesis is that the prior use of interferential current may improve exercise performance and collaborate with better clinical results, since patients with chronic low back pain have more difficulty performing the exercises due to pain and fear of a new, painful experience [22].

This will be a randomized controlled trial, with two arms and blinded evaluator, funded by São Paulo Research Foundation (FAPESP - 2013/17303-6), Brazil. The evaluations will be conducted at baseline, immediately after the intervention (active or placebo interferential current associated with Pilates exercises for six weeks) and six months after randomization.

## Methods/Design

### Participants, therapists and center

Participants with nonspecific chronic low back pain, aged between 18 to 80 years, of both sexes, and with pain intensity equal to or greater than 3 points, assessed by the Pain Numerical Rating Scale [23], will be recruited from the community through advertisements on websites, newspapers and TV shows. The inclusion criterion related to pain intensity was chosen, since participants with pain intensity inferior to 3 would not benefit from the clinical effect of the interferential current. Patients with any contraindications to perform exercises in accordance with the guidelines of the American College of Sports Medicine [24], with severe spinal diseases (such as fractures, tumors and inflammatory diseases), previous surgery on spine, nerve root compression, pregnancy, infection and/or skin lesions at the site of the application of the interferential current, with cancer, cardiac pacemaker, with changes in sensitivity or allergy in the region of electrode placement, under physical therapy treatment for chronic low back pain in the past six months and who are regularly involved with a Pilates program, will be excluded from the study. The eligibility criteria will remain unchanged after inclusion of the first participant in the study. In addition, the participants will be compensated for their transportation at the end of the study.

The participants will be taken care of by four physical therapists; two of them will be responsible for implementing the interferential current and assign participants to interventions ([name] and [name]) and two responsible for the Pilates exercises ([name] and [name]). The physical therapists responsible for implementing the Pilates exercises have specific training and a minimum of four years of experience with the method. In addition, these physical therapists will be blind with respect to which group the participant has been allocated. Participant assessment will be performed by another physical therapist that will not be involved in the treatment ([name]). The treatment sessions will be conducted at the outpatient Physical Therapy Clinic at Universidade da Cidade de São Paulo, in São Paulo, Brazil.

### Interventions

Participants will be randomly allocated in two intervention groups: 1) Group with active interferential current and Pilates exercises: this group will receive application of the active interferential current associated with the modified Pilates exercise; and 2) Group with sham interferential current and Pilates exercises: this group will receive the sham treatment of interferential current associated with the modified Pilates exercise. The treatment received by both groups will be carried out three times a week for six weeks consecutively. The sessions will be held individually. In the first two weeks, participants will be treated only with the active or sham interferential current to possibly reduce the pain and facilitate the performance of the exercises. In the next four weeks, immediately after the completion of electrotherapy sessions, the modified Pilates exercises will be added.

The interferential current will be delivered using a generator of alternating currents of medium frequency from the Brazilian Industry Medical Equipment (IBRAMED, São Paulo - SP, Brazil). Both groups will receive the bipolar mode, with two channels (4 self-adhesive electrodes, 50 × 90 mm) over the area of pain [25], with the following parameters: carrier frequency of 4 kHz; amplitude-modulated frequency (AMF) = 100 Hz; sweep frequency = 50 Hz; swing pattern 1:1 for 30 minutes [10]. In the Group with active interferential current and Pilates exercises, the physical therapist will be responsible for increasing the amplitude of the current until the participant reports feeling a “strong but comfortable tingling”. Every five minutes, the therapist will query the participant to ensure that the “strong but comfortable tingling” is maintained. In the case of decreased sensation, the amplitude of the current will be increased until the participant reaches the previous feeling [26]. In the Group with sham interferential current and Pilates exercises, all parameters will be adjusted as described, the audible alarm will be activated but the current amplitude will remain unchanged. The physical therapist responsible will ask if the participant is comfortable every five minutes, but without increasing the amplitude of the current.

After the first two weeks, participants in both groups will undergo a program of modified Pilates exercises that will be conducted on the floor and using the Cadillac, Reformer, Ladder Barrel and Step Chair equipment (Metalife, São José – SC, Brazil). In the first session of the Pilates exercises, participants will receive guidance through the method and will be trained to activate the powerhouse, that is to isometrically contract the transversus abdominis, multifidus and pelvic floor muscles associated with expiration. These muscle contractions will be performed throughout all exercises. The exercises have three levels of difficulty: basic, intermediary and advanced (Additional file 1). The level of difficulty will be set individually and the participants’ progress will be dependent on how well they perform 10 repetitions of the exercises without postural compensations [27, 28]. The strategy to prevent bias from the intervention is the individual monitoring of the participant by a trained physical therapist and the control of the level of exercise difficulty presented by the participant, since the treatment of chronic low back pain with the modified Pilates exercise has proven to be a safe intervention [29–31]. Moreover, the exercise program ends after the 6-week intervention, without any additional treatment, since both groups will receive the treatment according to the guidelines [1, 8] and the allocated interventions will not be modified. Participants that may need additional interventions will be referred to the outpatient Physical Therapy Clinic from the Universidade Cidade de São Paulo. During the study, the participants will be allowed to use their usual medication and this information will be monitored during the reassessments at six weeks and six months.

### Outcomes

The primary outcomes of the study are pain intensity, pressure pain threshold and disability at the 6-week follow-up after randomization. Secondary outcomes are global perceived effect, specific disability and kinesiophobia at the 6-week and 6-month follow-up after randomization, and pain intensity and disability at the 6-month follow-up after randomization.

Pain intensity will be evaluated using the Pain Numerical Rating Scale (0–10 points), with zero being “no pain” and 10 being “pain as bad as could be”. The participant must rate the average pain in the last seven days [32, 33].

Pressure pain threshold will be measured using the digital pressure algometer (Somedic Inc., Hörby, Sweden). Before data collection, the intra-rater reliability of the pressure pain threshold at the body landmarks used in the study were tested. The intra-rater reliability for the tibialis anterior muscle and the muscles of the lumbar region were 0.85 and 0.99, respectively, showing excellent intra-rater reliability. The algometry points will be marked using a measuring tape and pen. The participant will be seated in a chair without back support and the bony prominences over the vertebrae will be palpated bilaterally. The first landmark is located 5 cm laterally from the spinous processes of L3 [34] and the second landmark is 5 cm laterally from the spinous processes of L5 [35]. The third landmark is over the tibialis anterior muscle of the right leg in order to evaluate the segmental hyperalgesia [36, 37]. To measure the pressure pain threshold, the circular algometer probe will be positioned at an angle of 90° to the skin and pressed with a rate of about 50 kPa/s. The participant will be orientated to press and release a button when the sensation of pressure changes to a sharp pain. In this study, three repetitions of the measurement (in kPa) will be taken at each point, with an interval of 30 seconds between them [38]. The average of the three measurements will be used for analysis. The tests will be demonstrated two times using, as an example, the extensor muscles of the forearm of the dominant limb. If necessary, a third demonstration will be conducted. For participants without any pain at a pressure of 1000 kPa, this level of pressure pain threshold will be used for analysis.

The Roland Morris Disability questionnaire will be used to measure disability of the participant with regard to the physical limitations caused by pain in the lumbar spine in the last 24 hours. It is a 24-item questionnaire with each answer scaled either “yes” or “no” and is related to the activities of daily living of the participant - each affirmative response corresponds to one score. The final score is determined by the sum of all the scores obtained for each question. Scores close to zero are the best results (lower disability) and scores near 24 are the worst results (higher disability). Scores greater than 14 points are indicative of severe impairment of the back [32, 39–41].

The global perceived effect will be evaluated by the Global Perceived Effect scale that compares the onset of symptoms with the last few days. It is an 11-point numerical scale, ranging from -5 to 5, with -5 being “vastly worse”, 0 being “no change” and 5 meaning “completely recovered”. Higher scores indicate greater recovery from the condition [32, 42].

Specific disability will be assessed using the Patient-Specific Functional scale and the participants will be asked to identify three important activities that they feel incapable of or have difficulty performing due to chronic low back pain. The participants will indicate on an 11-point scale (0–10) how capable they feel performing specific activities, with 0 representing “unable to perform the activity” and 10 representing “able to perform the activity at preinjury level”. The average of the scores for the three activities will be calculated. The higher the score, the greater the functional ability of the participant [32, 43].

Kinesiophobia will be measured using the Tampa scale for Kinesiophobia that comprises 17 questions that address pain and symptom severity. The scores range from 1 to 4 points, where 1 represents “strongly disagree”, 2 represents “partially disagree”, 3 represents “partially agree”, and 4 represents “strongly agree”. For the overall final score, the scores for questions 4, 8, 12, and 16 must be inverted. The final score ranges from 17 to 68 points, with higher scores indicating a higher degree of kinesiophobia [44–46].

All outcome measures were previously adapted cross-culturally into Brazilian-Portuguese language, and the measurement properties of these instruments were tested with participants with low back pain in Brazil [32, 39, 40, 44, 45], and the results were acceptable and equivalent to those of the original versions in English.

### Procedures

Participants with nonspecific chronic low back pain will be recruited for the study. The participants will be assessed by a blinded evaluator, with prior training and experience in the field, for confirmation of eligibility criteria. In addition, demographic and anthropometric data will be obtained and other information such as the use of pain medications and the realization of any other treatment for low back pain. Eligible participants will be informed about the objectives and procedures of the study and following, the primary and secondary outcomes will be collected. Written informed consent will be obtained from all participants.

Randomization will be performed by a researcher not involved in the recruitment and treatment of the participants ([name]), using the random number generation from Microsoft Excel for Windows. The allocation will be concealed by using consecutively numbered, sealed, opaque envelopes. After evaluation, eligible participants will be referred to the physical therapists responsible for the electrotherapy treatment that will randomly distribute the participants in the treatment groups.

The primary and secondary outcomes will be assessed at three different terms: baseline, 6-week follow-up and 6-month follow-up. In addition, at the last two assessments the participants will be instructed to refrain from providing treatment information to the evaluator. Only the pressure pain threshold obtained with the algometry will be performed at baseline and at the 6-week follow-up. This procedure aims at minimizing the loss of participants on returning visits at the 6-month follow-up for assessment, since the algometry requires the physical presence of the participant while the questionnaires and scales can be reapplied over the phone. Due to the nature of the intervention, it will not be possible to blind the participants and the therapists responsible for the implementation of the interferential current. Participant recruitment began in October 2013 and has a target date of February 2015 for completion. Table 1 shows the timeline of the study.

**Table 1 Tab1:** **Timeline for the schedule of enrolment, interventions, and assessments**

Outcomes	Enrolment	Before randomization	Intervention period (6 weeks)	6-week follow-up after randomization	6-month follow-up after randomization
Eligibility criteria	X				
Demographic data	X				
Informed consent	X				
Primary outcomes					
Pain intensity		X		X	
PPT		X		X	
Disability		X		X	
Secondary outcomes					
Pain intensity					X
Disability					X
GPE		X		X	X
Specific disability		X		X	X
Kinesiophobia		X		X	X
Interventions					
Active IC + Pilates			X		
Sham IC + Pilates			X		

PPT: Pressure pain threshold; GPE: Global perceived effect; IC: Interferential current.

### Data analysis

A committee for data monitoring will consist of two authors from the study ([name] and [name]) that are not involved with data collection and have no conflict of interest. Auditing of the randomization process of the participants in the intervention groups will be held monthly. Statistical analysis will be performed by a researcher who will receive the data encoded ([name]). All data will be double-entered prior to the analysis. The mean effects of the interventions and the group differences for all the outcomes will be calculated using linear mixed models. The linear mixed models include terms for the treatment groups, time, and interaction terms “treatment group” and “time”. The term “time” will be coded as three categorical variables: baseline, 6-week follow-up and 6-month follow-up. No interim analysis will be performed. The analysis will follow the intention-to-treat principles. If a participant abandons the treatment, no additional outcome will be collected and the missing data will not be replaced. For all statistical analyses, the level of confidence will be set at 5%. The IBM Statistics Package for the Social Science (SPSS) version 19 for Windows will be used in the analysis.

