### Sample size calculation

This study is designed to detect a clinically important difference between groups of one point in the Pain Numerical Rating scale (estimate for standard deviation = 1.84 points), 100 kPa in the pressure pain threshold measured with the algometer (estimate for standard deviation = 110 kPa) and four points in disability assessed by the Roland-Morris Disability questionnaire (estimate for standard deviation = 4.9 points). The following specifications will be considered: α = 0.05, statistical power of 80% and follow-up loss of 15%. The sample size calculation resulted in 148 participants that will be randomly allocated into two intervention groups.

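### The mixed model leaves the pre-randomisation group difference free, so either reading of the 6-week effect is less precise than a baseline-adjusted estimate

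*Protocol article*

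**What the plan says.** Under Data analysis, the article says "The mean effects of the interventions and the group differences for all the outcomes will be calculated using linear mixed models". It then lists the fixed effects: "The linear mixed models include terms for the treatment groups, time, and interaction terms", that is, group, time and group by time. Time "will be coded as three categorical variables: baseline, 6-week follow-up and 6-month follow-up". Nothing enters baseline as a covariate, omits the group main effect or sets the baseline means equal. The contrast that gives the treatment effect is not named.

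Under Outcomes, "The primary outcomes of the study are pain intensity, pressure pain threshold and disability at the 6-week follow-up after randomization". Under Procedures, baseline values are obtained at the eligibility visit: "Eligible participants will be informed about the objectives and procedures of the study and following, the primary and secondary outcomes will be collected". Allocation follows, and Table 1 places the baseline measurements in a column before randomisation.

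Sample size calculation plans for "one point in the Pain Numerical Rating scale (estimate for standard deviation = 1.84 points") and "100 kPa in the pressure pain threshold measured with the algometer (estimate for standard deviation = 110 kPa"), and for four points on the Roland-Morris questionnaire with SD 4.9. It does not say whether these SDs are for a single score or for change, and it gives no correlation between baseline and follow-up.

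**The concern.** Baseline precedes randomisation, so any group difference there is chance. A model with a free group effect at baseline estimates a quantity already known to be zero in expectation, and loses precision by doing so.

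Two 6-week contrasts can be read from the model. The group by 6-week interaction is a change-score comparison and carries the whole chance baseline difference into the effect. The group difference at 6 weeks leaves the baseline information largely unused. Either way, intervals for the primary outcomes are wider than the collected data require. For pain, the outcome that drives the sample size, one combination of assumptions would also take power below the planned 80%.

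**Working it through.** **Inputs.** From Sample size calculation: differences and SDs as above, alpha 0.05 (two-sided assumed), 80% power, 15% loss, 148 participants. Evaluable per arm: 74 × 0.85 = 62.9. Assumed: correlation r between baseline and 6 weeks, and k = baseline SD / 6-week SD.

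**The plan's own figure.** For pain, n per arm = 2 × (1.960 + 0.842)² × 1.84² / 1² = 53.1, so 54 (55 by t-test). Dividing by 0.85 gives 64 to 65 per arm, or 128 to 130 in total. The stated inputs do not reproduce 148. That is a separate matter, and nothing below depends on it except that 74 per arm is taken as given.

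**What the model estimates.** A generalised least squares fit of the stated model to simulated complete data (63 per arm, three visits, r = 0.3) gave a 6-week interaction of -0.1815, identical to the raw difference in mean change. Its standard error was 0.388, against 0.313 with a common baseline mean. At r = 0.5 the standard errors were 0.328 and 0.284.

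**Variances**, in units of the squared 6-week SD:
- change: 1 + k² - 2rk, which is 2(1 - r) when k = 1
- 6-week difference: 1
- baseline-adjusted: 1 - r²

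The change-to-adjusted ratio is 1 + (r - k)²/(1 - r²). It is never below 1, and equals 1 only when r = k. With k = 1 it is 2/(1 + r). The ratio for the 6-week difference is 1/(1 - r²), whatever k is.

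| r | change / adjusted (k = 1) | 6-week difference / adjusted |
|---|---|---|
| 0.3 | 1.54 | 1.10 |
| 0.5 | 1.33 | 1.33 |
| 0.7 | 1.18 | 1.96 |

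**Power for 1 point of pain, 62.9 per arm, 1.84 as a single-score SD, k = 1:**

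| r | change | 6-week difference | adjusted |
|---|---|---|---|
| 0.3 | 73.1% | 86.2% | 89.2% |
| 0.5 | 86.2% | 86.2% | 94.1% |
| 0.7 | 97.6% | 86.2% | 98.9% |

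The change contrast reaches 80% at r of about 0.41. Between there and r = 0.5 it lies between 80% and 86%.

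**1.84 as the SD of change (k = 1):** power for change is 86.2% at any r; adjusted power is 96.6%, 94.1% and 91.1% at r = 0.3, 0.5 and 0.7.

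**Smaller baseline SD.** With k = 0.8 and r = 0.3, the change variance is 1 + 0.64 - 0.48 = 1.16. The ratio is 1.16/0.91 = 1.27 rather than 1.54, and power for change is about 81%. The correlation at which change power reaches 80% falls from about 0.41 to about 0.29.

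**Other primary outcomes.** With the change contrast, k = 1, single-score SDs and r as low as 0.2, power is 98% for pressure pain threshold and 95% for disability.

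**The case against.** The published model is common, valid and unbiased under randomisation, and contains no contradiction. An analysis plan that is not shown may name the contrast. All of that stands, so this is a point about efficiency and sensitivity to chance imbalance, of a size that the article does not let one fix. It does not dispose of the point: the article states the model terms and makes baseline a level of time, and both natural contrasts from that model lose precision.

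Three stronger readings are tempting and not supported.
- *The 6-week effect is a change-score contrast.* The article speaks only of group differences, so this is one of two readings.
- *The trial is underpowered.* This requires a change contrast, a single-score SD of 1.84 and a low correlation together, none of which the article states, and it would touch pain only.
- *The entry requirement of pain of at least 3 makes the change-score loss worse by lowering the correlation.* Selection on baseline X leaves the slope b and residual variance unchanged and shrinks Var(X). The ratio 1 + (1 - b)² Var(X)/Var(e) therefore falls, and the cut-off reduces the penalty.

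The Ethics section also commits to no change of analysis after the first enrolment, and the Discussion reports 116 participants already assessed at baseline. That makes a documented amendment necessary. It does not rule one out, since no interim analysis is planned and the analyst receives encoded data.

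**Conclusion.** The point holds as a loss of precision, not as bias or an invalid test. The baseline group difference is left free without need, and the primary contrast is not named. With equal SDs, the variance excess over an adjusted estimate is 54%, 33% and 18% for the change contrast and 10%, 33% and 96% for the 6-week difference, at r = 0.3, 0.5 and 0.7. The correlation is assumed throughout. The change penalty is smaller if the baseline SD is below the follow-up SD, as the pain cut-off may cause.

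Power for pain is in doubt only under the joint conditions above. If the 6-week difference is used, or if 1.84 is the SD of change, it is about 86%; adjustment for baseline raises it in each case shown. The equality of the interaction with raw change is exact for complete data and approximate with dropout.

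**What to change.** By a dated, documented amendment before unblinding, adopt one of these:
- **Common baseline mean:** drop the group main effect; keep time, group by 6 weeks and group by 6 months, with an unstructured covariance.
- **Baseline as covariate:** model the follow-up visits with baseline, baseline by time, time, group and group by time.

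Pressure pain threshold has no 6-month visit, so its model uses 6 weeks as the only follow-up. The two versions are near-equivalent but not identical when follow-up data are missing, so one should be chosen in advance.

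Name the group contrast at 6 weeks as the primary estimate, and say whether the planning SDs are for single scores or for change. The published model can stay as a supporting analysis.

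The cost is the amendment, because the Ethics section says that the analysis will not change, and a small edit to the model syntax. No new data or participants are needed.

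### Outcome collection stops when a participant abandons treatment, so the intention-to-treat effect at 6 weeks rests on those who stayed plus an untestable missing-at-random assumption

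*Protocol article*

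**What the plan says.** In the protocol article, two consecutive sentences under Data analysis bear on this point. The first is "The analysis will follow the intention-to-treat principles". The second is "If a participant abandons the treatment, no additional outcome will be collected and the missing data will not be replaced".

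The timing comes from three other places:
- Under Interventions, treatment "will be carried out three times a week for six weeks consecutively".
- Under Outcomes, "The primary outcomes of the study are pain intensity, pressure pain threshold and disability at the 6-week follow-up after randomization".
- Table 1 shows no outcome assessment between baseline and the 6-week visit.

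On the analysis, the article says "The mean effects of the interventions and the group differences for all the outcomes will be calculated using linear mixed models". The terms are group, time and their interaction, and time "will be coded as three categorical variables: baseline, 6-week follow-up and 6-month follow-up".

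Procedures explains why algometry is left out at 6 months: it needs the participant to attend, whereas "the questionnaires and scales can be reapplied over the phone".

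The sample size allows for 15% loss. The closing status report gives 90 participants assessed at 6 weeks and five lost by then, without arms or reasons.

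**The concern.** An intention-to-treat effect compares everyone randomised, whatever treatment they went on to receive. It therefore needs the outcomes of people who stopped. Here those outcomes are missing by rule, not by accident. The article states this rule outright, so it is not a detail left for an analysis plan to supply, and no later analysis can recover values that were deliberately not collected.

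The rule falls exactly on the primary comparison. Treatment finishes at the primary time point, so every act of abandonment comes before it. With no intermediate visit, the model knows only the baseline of someone who left. It cannot see a poor response in weeks 1 to 5 that led them to leave. In effect it predicts their 6-week score from people in the same arm who stayed in treatment. If those who leave do differently, the estimated difference is not the effect in all randomised participants, and the error can go either way.

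**Working it through.** **The plan's own figure.** For pain, the inputs are a difference of 1 point, SD 1.84, α = 0.05 (two-sided assumed) and 80% power. Per arm, n = 2 × (1.960 + 0.842)² × 1.84² / 1² = 53.1, so 54. With 15% loss, 54 / 0.85 = 63.5, so 64 per arm and 128 in all. The stated 148 (74 per arm) is not reproduced. It is larger than the inputs require, and nothing below depends on the gap.

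**Power.** After 15% loss, 74 × 0.85 = 62.9, about 63 per arm.
- With 63 per arm: SE = 1.84 × √(2/63) = 0.328, and power = Φ(1/0.328 − 1.96) = 86%.
- With all 74 per arm: SE = 0.302, and power = 91%.

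Both exceed 80%, so what remains is a question of bias.

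**Who lacks data.** 15% of 148 is about 22 participants. Loss so far is 5 / (90 + 5) = 5.3%, assuming that those 95 were the ones due.

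**Bias of a simple contrast of observed 6-week means.** Let d be the proportion lost in an arm and g the mean 6-week score of those lost minus that of those observed. The arm's true mean is its observed mean plus d × g. For the active-minus-sham contrast (negative favours active):

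observed − all randomised = d_sham × g_sham − d_active × g_active

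A positive value understates the benefit of active current. All values of d and g below are assumptions, because the documents give neither by arm.

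| Loss, active / sham | Gap g (pain points) | Error | Direction |
|---|---|---|---|
| 15% / 15% | 2 in both arms | 0 | none |
| 10% / 20% | 2 in both arms | +0.20 | understates |
| 5% / 25% | 2 in both arms | +0.40 | understates |
| 20% / 10% | 2 in both arms | −0.20 | overstates |
| 15% / 15% | 1 in active only | −0.15 | overstates |
| 3.5% / 7.0% (near the loss so far) | 2 in both arms | +0.07 | understates |

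The fifth row has a plain reading: if people who stop active treatment lose a 1-point benefit, an observed effect of 1.0 corresponds to 0.85 in all randomised.

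**How far the mixed model repairs this.** A simulation used 74 per arm, SD 1.84, a true effect of −1.0 and a baseline to 6-week correlation of 0.3 to 0.5. Loss was random in the active arm, with probability 1/(1 + e^2.2), about 10%. In the sham arm it rose with the score: the log-odds were −2.2 + 0.9 × (score − mean), about 18% lost on average. The model was fitted by maximum likelihood to the two visits.

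| Sham loss depends on | Observed cases only | Mixed model |
|---|---|---|
| Baseline score | −0.87 to −0.79 | −0.99 |
| 6-week score | −0.60 to −0.61 | −0.63 to −0.69 |

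The formula agrees with the second row. Under that mechanism those lost score about 2.2 points worse, and 0.18 × 2.2 = 0.40, which is the distance from −1.0 to −0.60. So the model removes the bias when baseline explains the loss, and little of it when people leave because of their current state.

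**The case against.** The strongest reply is that the planned model already handles this. A reader might infer that the primary analysis is completers-only. The article does not support that: baseline is a level of the response, so a participant who leaves still contributes, and a likelihood-based model is valid if missingness depends only on observed data. Not replacing missing values simply means no imputation, which suits such a model and is no fault. The rule also concerns people who abandon treatment; nothing says that those who merely miss sessions are dropped. All of this stands. It narrows the problem to an untestable assumption but does not remove it.

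A reader might also infer that sham participants are likelier to leave because they have no exercise in the first two weeks. Under Interventions neither arm exercises then, so this is not a difference between arms. Differential loss is possible but not shown.

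Nor may all 22 tolerated losses be charged to this rule: the 15% is for loss to follow-up of any kind, and the five losses so far may not be abandonments. Loss is low to date, and the bias figures rest on chosen inputs.

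Two practical objections remain. Phone collection is described for 6 months only, and algometry cannot be done that way. The Ethics section rules out changing eligibility, outcomes or analysis after the first enrolment. Continued follow-up changes none of these three and supplies the data that the promised analysis needs.

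**Conclusion.** The point holds in this form: the collection rule conflicts with the intention-to-treat statement beside it. By design, no one who abandons treatment has a primary outcome value. The 6-week effect is estimated from those who did not abandon, plus the baselines of those who did, under a missing-at-random assumption that the collected data cannot test.

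The possible error on the pain scale runs from none (equal loss, equal gap) to about 0.2 to 0.4 points against the 1-point target, for a 2-point gap with loss of 10% against 20% or 5% against 25%. It would be under 0.1 point in the tabulated case near the current 5.3% loss. Its sign depends on which arm loses more people and how they fare. These are illustrations, since loss by arm and the scores of those lost are not reported. That the rule leaves these outcomes unmeasured follows from the text alone and needs none of these assumptions.

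**What to change.** Replace the sentence on abandonment with, for example:

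> Participants who stop treatment remain in follow-up unless they withdraw consent. Questionnaires and scales are collected at 6 weeks and 6 months after randomisation regardless of sessions attended, by phone if needed. Pressure pain threshold is measured at 6 weeks where the participant will attend. All data are analysed in the randomised group.

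This extends to the 6-week visit the phone route that Procedures gives for 6 months. Attempt 6-month contact with those already lost. Where data are still missing, state the missing-at-random assumption and qualify the intention-to-treat claim accordingly.

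The cost is a short amendment and a few extra calls. Some gaps will remain: pressure pain threshold may stay missing for those who will not attend, and missed 6-week values of earlier dropouts cannot be recovered. The collection rule would also change partway through, with 116 of 148 participants already evaluated at baseline, so the date of the change must be reported. Only 30 had reached the 6-month assessment, so most of that follow-up can still be protected, as can the 6-week visits of later entrants.
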